#### Evaluating the cost-effectiveness of interventions

The cost-effectiveness of implementing the IP-SDM care model will be evaluated over a study period of six months.

From a societal perspective, costs will include those borne by women and health insurance as well as those borne by the hospital. The costs borne by women and health insurance will be estimated based on the predicted values from the regression analysis described above, using data collected from questionnaires. The costs borne by hospitals will be accounted for using the time-driven activity-based costing (TDABC) method [40]. TDABC is a costing method that utilizes the time needed to complete the process to produce a product or deliver a service. In healthcare settings, TDABC is often implemented using seven-step approach, as follows: select the health condition; define the care delivery value chain; develop process maps that include each activity in patient care delivery, and incorporate all direct and indirect capacity-supplying resources; obtain time estimates for activities and resources used; estimate of all direct and indirect resources involved in care delivery; estimate the capacity of each resource and calculate the capacity cost rate (e.g., a cost per unit of time); calculate the total cost of patient care by multiplying the total time of care delivery by the capacity cost rate [41].

In the cost-effectiveness analysis, the effectiveness will be calculated based on the number of women who score 13 or higher on the EPDS at 6 months post-baseline. To compare the cost-effectiveness of between the intervention and control groups, the incremental cost-effectiveness ratio (ICER) will be calculated as the difference in cost between the two groups divided by the difference in their effectiveness.

In addition, the utility will be calculated based on QALYs converted from health-related quality of life as measured by the SF-6D at 6 months post-baseline. ICER will then be calculated as the difference in cost between the intervention and control groups divided by the difference in their QALYs.

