**Secondary outcome indicators**		
	Shared decision-making	Shared decision-making will be measured based on an adapted decision expectancy scale (control preference scale, CPS). This scale was originally used to measure patients’ willingness to participate in health care decision-making. In its adaptation, it can also measure patients’ actual participation in decision making in a given decision situation and can classify patients into three types: active decision makers, negative decision makers, and shared decision makers. This is one of the most commonly used and concise tools for measuring shared decision-making.
	Mental health service utilization	A self-administered questionnaire will be used to investigate whether mothers are diagnosed by a psychiatrist with a mental disorder such as PND and the utilization of subsequent mental health services, including all mental health services such as counseling, psychotherapy, and psychiatric services received by mothers at the study site and other institutions or settings (e.g., number of visits, number of counseling sessions, length of medication, etc.).
	Cost	A self-administered questionnaire will be used to measure the costs associated with maternal mental health service seeking. The self-administered scale will be developed with reference to the Treatment Inventory of Costs in Psychiatric Patients and will consist of: direct medical costs, including the costs of maternal psychiatric services, psychotherapy, counseling, etc. (including maternal and health insurance paid costs); direct non-medical costs, including transportation and accommodation fees for maternity and their companions seeking mental health services; indirect costs, including labor losses such as lost wages for maternity and their companions as a result of seeking mental health services. As the related costs are incurred within six months, no discounting is required. Self-administered questionnaires will also be used to measure the cost of conducting the interprofessional shared decision-making model and subsequent mental health services, including mainly depreciation of fixed assets and staff labor costs, among medical staff and hospital administrators.

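### For charged on-site mental health services, the societal cost adds the fee to the hospital production cost that the fee pays for, and no netting is stated

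*Protocol article*

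**What the plan says.** Under Evaluating the cost-effectiveness of interventions, the protocol article takes a societal perspective and defines the total as a sum: "costs will include those borne by women and health insurance as well as those borne by the hospital". The women's and insurers' part comes from questionnaire data through regression predictions. For the hospital part, "The costs borne by hospitals will be accounted for using the time-driven activity-based costing (TDABC) method".

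The Cost row of Table 1 gives the content of each part:

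- **Women and insurers:** "direct medical costs, including the costs of maternal psychiatric services, psychotherapy, counseling, etc. (including maternal and health insurance paid costs"), plus travel, accommodation and lost wages.
- **Hospital:** "the cost of conducting the interprofessional shared decision-making model and subsequent mental health services, including mainly depreciation of fixed assets and staff labor costs".

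The neighbouring Table 1 row on mental health service utilization covers "psychiatric services received by mothers at the study site and other institutions or settings". The last of the TDABC steps listed is to "calculate the total cost of patient care by multiplying the total time of care delivery by the capacity cost rate".

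For the first ratio, "the incremental cost-effectiveness ratio (ICER) will be calculated as the difference in cost between the two groups divided by the difference in their effectiveness". A second ratio divides the cost difference by the difference in QALYs.

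**The concern.** From a societal perspective a resource counts once. A fee that a woman or her insurer pays for counselling at the study hospital is a transfer to the hospital. It pays for the staff time and assets that TDABC values directly. If both amounts are added, the fee sits on top of the resource cost it covers.

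The overlap would cancel in a between-arm difference only if paid on-site use were equal in the two arms. The Background hypothesizes that the model has a positive effect on mental health service utilization, and on-site outpatient counselling is itself listed as part of the care model under Intervention. The overlap therefore lies in a cost item on which the arms may well differ. Cost-effectiveness is a stated purpose of the trial, and the Discussion intends it to support dissemination.

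**Working it through.** The plan states no cost figure, so there is none to reproduce. The check is an accounting one.

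**Step 1: what each part contains.**

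| Item | Women and insurers (questionnaire) | Hospital (TDABC) |
|---|---|---|
| Charged on-site service | fee F (not excluded) | production cost C |
| Uncharged contact, e.g. a nurse call without a fee | 0 | C |
| Off-site service | fee | 0 |
| Travel, accommodation, lost wages | counted | 0 |
| Delivering the shared decision-making model, if uncharged | 0 | counted |

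Only the first row has an entry in both columns for the same resource.

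**Step 2: cost per charged on-site service.**

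- As written: F + C.
- Counted once: C. Equivalently, with the fee netted from the hospital's cost, F + (C − F) = C.
- Excess: F. Ratio to true cost: (F + C)/C = 1 + F/C.

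The documents give neither F nor C. With C = 100 assumed:

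| F as share of C (assumed) | As written | Counted once | Ratio |
|---|---|---|---|
| 0% | 100 | 100 | 1.00 |
| 25% | 125 | 100 | 1.25 |
| 50% | 150 | 100 | 1.50 |
| 75% | 175 | 100 | 1.75 |
| 100% | 200 | 100 | 2.00 |
| 120% | 220 | 100 | 2.20 |

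**Step 3: incremental cost.** Let S be the uncharged cost per woman of delivering the model, and d the difference in charged on-site services per woman (intervention minus control). As written, the incremental cost is S + d(C + F). Counted once, it is S + dC. The error is d × F. With S = 50 and C = 100 assumed:

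| d | F/C | As written | Counted once | Ratio |
|---|---|---|---|---|
| 0.5 | 25% | 50 + 0.5 × 125 = 112.5 | 100 | 1.125 |
| 0.5 | 50% | 125 | 100 | 1.25 |
| 0.5 | 100% | 150 | 100 | 1.50 |
| 1 | 25% | 175 | 150 | 1.17 |
| 1 | 50% | 200 | 150 | 1.33 |
| 1 | 100% | 250 | 150 | 1.67 |
| 2 | 25% | 300 | 250 | 1.20 |
| 2 | 50% | 350 | 250 | 1.40 |
| 2 | 100% | 450 | 250 | 1.80 |

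Off-site care, travel and lost wages are left out of this table. Any between-arm difference in them would enter both columns equally and change the ratio, but not the error d × F.

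**Step 4: direction.** The error d × F has the sign of d. If d = 0 it vanishes. If d = −0.5 and F = 50, the plan gives 50 − 0.5 × 150 = −25 where the correct figure is 50 − 0.5 × 100 = 0, so the intervention looks cheaper than it is. The denominators of the two ratios do not contain cost, so the error passes into each ratio as d × F divided by the difference in effectiveness or in QALYs.

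**The case against.** The strongest reply is that the plan divides costs by who bears them. Read literally, a cost the hospital has recovered from a patient or insurer is not borne by the hospital, so the parts could add up without overlap. A journal article may also leave a netting rule to a fuller document. This reading is possible. However, the stated hospital items are labour and depreciation, which are gross, and Table 1 expressly extends them beyond the shared decision-making model to later mental health services. The problem is a stated rule that gives the wrong total, and one sentence is needed even if netting is intended.

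Two evidential limits stand. The quoted TDABC step belongs to a general description of the method, so it supports a gross reading without proving it. The reference to the study site is in the utilization row. That on-site payments fall under the Cost row follows from the absence of any exclusion there.

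Two stronger readings are tempting. A reader might infer that every on-site visit is counted twice. The documents do not support that: only the fee is duplicated, the article does not say which on-site contacts are charged, and exact doubling needs a fee equal to production cost. A reader might also infer that both ratios are necessarily biased against the intervention. That needs paid on-site use to rise. The Background calls the effect of shared decision-making on resource use controversial, the decision aid includes follow-up without treatment among its options, and care may go off site by referral. The hypothesis makes a rise the expected case, not a known one.

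**Conclusion.** The concern holds in this form: as written, the fee for a charged on-site service is added to the production cost it pays for. The excess per service equals the fee. It is 25% to 100% of true cost if fees are 25% to 100% of production cost, and nil for uncharged contacts. Under the further assumptions in Step 3, incremental cost is overstated 1.125-fold to 1.8-fold. All these sizes rest on assumed prices and assumed differences in use, so the actual size cannot be computed from the documents.

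The direction depends on paid on-site use: against the intervention if it rises, in its favour if it falls, and no effect on the ratios if it is equal. Severity is moderate. Cost is a secondary outcome, and the primary outcome, decisional conflict at one month, is unaffected.

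**What to change.** State that each service at the study hospital is valued once. Either of two rules does this:

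- Use the TDABC production cost for on-site services, and exclude women's and insurers' payments for those services as transfers.
- Use payments for on-site services, and limit TDABC to delivery of the shared decision-making model plus any part of on-site production cost that fees do not cover.

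The two rules agree where the fee does not exceed production cost. The choice should be fixed before analysis. Under either rule, use payments as the cost of off-site care and keep travel, accommodation and lost wages. Payments can be reported separately from a payer perspective.

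The cost questionnaire, which Table 1 describes as still to be developed, should record on-site and off-site payments separately. Without that split, the overlap may not be removable after data collection.

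The cost is one accounting rule and a slightly longer questionnaire. Sample size, primary outcome and trial conduct do not change.

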### ④ Sample size

The primary outcome indicator in this study is the level of decisional conflict at one month after baseline, which is a continuous variable. For the comparison of continuous variable outcome indicators in randomized clinical trials, the sample size can be estimated by the following equation.

Sample size of each group:

$$n = \frac{{2 \times {{({z_{(1 - \alpha /2)}} + {z_\beta })}^2}}}{{{{(\frac{\Delta }{\sigma })}^2}}}$$

Among them, α is set to 0.05, the Z_(1−α/2)_ takes the value of 1.96, while β is set to 0.80, and Z_β_ takes the value of 0.84. ∆/σ is the effect value and is set to 0.3 with reference to previous literature [37], resulting in a required sample size of 174 participants per group. Considering that some of the study participants (assumed to be ≤ 15%) might drop out of the study, the total target of recruiting participants is set at 410 after appropriate expansion of the sample size, and the intervention and control groups are assigned in a 1:1 ratio.

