	Depressive symptoms	Women’s depressive symptoms will be measured by the EPDS, a 10-item maternal self-report of depression over the past 7 days. Higher EPDS scores indicate more severe depression. The EPDS is the most commonly used screening tool for perinatal depression in maternal health care and has good reliability.
	Health-related quality of life	Health-related quality of life will be measured based on the SF-6D, a utility measurement tool created based on the MOS 36-item short-form health survey (SF-36), which is widely used to measure health-related quality of life and can be used to calculate utility values. The SF-6D health classification system consists of 6 dimensions: somatic functioning, role limitation, social functioning, pain, mental health, and vitality. Previous literature has shown that the SF-6D works well in measuring health-related quality of life in mental health and that the SF-6D is more likely to capture the effects of interventions than the EQ-5D in the area of perinatal mental health.

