**Control variables**		
	Decision-making preferences	Decision-making preferences will be measured by the Control Preference Scale, which is commonly used to measure patients’ willingness preferences to participate in healthcare decision-making. The scale consists of 5 entries that can classify patients into 3 types: active decision makers, negative decision makers, and shared decision makers.
	Mental health literacy and stigma	The Multicomponent Mental Health Literacy Measure (MMHLM), which is commonly used internationally, is applied in this study to measure maternal mental health literacy and stigma. The 22-item MMHLM, which contains three dimensions of knowledge, beliefs, and resources, has good reliability and validity, is suitable for assessing mental literacy in adult populations, and is also a good predictor of mental health service utilization behavior. The Chinese version of the questionnaire has been tested for reliability and validity in a domestic population.

**Baseline Survey**: After obtaining informed consent, a member of the research team will conduct a baseline survey. This survey will include basic maternal personal information (e.g., age, education, marital status, family health history, health insurance), level of decisional conflict, history of mental health service utilization, mental health literacy and stigma, and decisional preferences. Among them, basic demographic and health information (e.g., family health history) will be compared with electronic health records for confirmation.**Follow-Up Survey**: Follow-up surveys will be conducted at one, three, and six months after baseline. These surveys will include measures of shared decision-making (at one month only), decisional conflict, depressive symptoms, mental health service utilization, and associated costs. The primary outcome of this study is the level of decisional conflict one month after baseline.

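### As written, QALYs rest on one SF-6D measurement at month 6, which does not determine a six-month QALY difference, and the text is inconsistent on when the SF-6D is collected

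*Protocol article*

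**What the plan says.** Four places in the protocol article bear on this.

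- **Evaluating the cost-effectiveness of interventions** sets the horizon: "The cost-effectiveness of implementing the IP-SDM care model will be evaluated over a study period of six months". For the cost-utility part it states that "the utility will be calculated based on QALYs converted from health-related quality of life as measured by the SF-6D at 6 months post-baseline", and that "ICER will then be calculated as the difference in cost between the intervention and control groups divided by the difference in their QALYs". It names no earlier utility measurement, no area-under-the-curve calculation and no baseline adjustment.
- **Abstract and Table 1** make health-related quality of life a secondary outcome. Table 1 says "Health-related quality of life will be measured based on the SF-6D, a utility measurement tool" but gives no time points.
- **⑥ Measurements, baseline survey** lists personal information, followed by "level of decisional conflict, history of mental health service utilization, mental health literacy and stigma, and decisional preferences". The SF-6D is not named.
- **⑥ Measurements, follow-up survey** gives the timing: "Follow-up surveys will be conducted at one, three, and six months after baseline". On content it says: "These surveys will include measures of shared decision-making (at one month only), decisional conflict, depressive symptoms, mental health service utilization, and associated costs". The SF-6D is again not named.

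The same section refers to Fig. 3 for the timeline of assessments. That figure was not available to this review.

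**The concern.** There are two linked problems.

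First, the text does not agree with itself. Table 1 makes the SF-6D an outcome without timing, the survey lists leave it out, and the cost-effectiveness section assumes it exists at month 6.

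Second, even if the month-6 measurement is secure, it is not enough. A QALY is utility accumulated over time, so the six-month difference depends on how the arms separate between baseline and month 6. In this trial a smooth path cannot be taken for granted:

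- The intervention acts early. The decision aid comes before the consultation, coaching follows one week after it, and the primary outcome is read at one month.
- Women enter during pregnancy or in the first weeks after delivery, so delivery falls inside the observation window for some of them, at varying times.

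The cost-utility ICER is at stake. This goes beyond detail that an article may leave to an analysis plan, because no later analysis can recover utilities that were not collected.

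**Working it through.** **The plan's own figures.** The article states no QALY or utility value, so there is none to reproduce. The only figure borrowed below is the group size. The article's formula gives 2 × (1.96 + 0.84)² / 0.3² = 15.68 / 0.09 = 174.2, reported as 174 per group. Then 174 / 0.85 = 204.7, rounded up to 205 per group, or 410 in total. Both match and neither is in dispute.

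**Inputs.** Times of 0, 1, 3 and 6 months are the article's contact points. The horizon is 0.5 year. The utility differences, utility SDs and cost difference are assumptions.

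**Formula.** The trapezoid rule over 0, 1/12, 3/12 and 6/12 year gives the between-arm differences at months 0, 1, 3 and 6 the weights 1/24, 3/24, 5/24 and 3/24 year, which sum to 0.5.

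**One month-6 difference, several paths.** Take a difference of 0.04 at month 6 (range 0.02 to 0.06) and equal baselines. The last column uses an assumed cost difference of 1,000 units and the 0.04 case.

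| Path | Calculation for 0.04 | QALY difference (range) | ICER |
|---|---|---|---|
| Appears only after month 3 | 0.04 × 3/24 | 0.005 (0.0025 to 0.0075) | 200,000 |
| Linear from baseline | 0.04 × 0.5 / 2 | 0.010 (0.005 to 0.015) | 100,000 |
| Full from month 1 | 0.04 × 11/24 | 0.0183 (0.0092 to 0.0275) | 54,545 |
| 1.5 times as large at months 1 and 3 | 0.06 × 8/24 + 0.04 × 3/24 | 0.025 (0.0125 to 0.0375) | 40,000 |
| Month-6 value × 0.5 year | 0.04 × 0.5 | 0.020 (0.010 to 0.030) | 50,000 |

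The first four rows share the same month-6 measurement and differ five-fold (0.025 / 0.005).

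**An early benefit that fades.** Let the arms be equal at baseline and month 6 but 0.03 apart at months 1 and 3. The gain is 0.03 × (3/24 + 5/24) = 0.010 QALY, while the month-6 difference is 0.

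**Chance baseline imbalance.** With an assumed SD of 0.12 and 174 per arm, the SE of the baseline difference is 0.12 × √(2/174) = 0.0129. In a two-point trapezoid (months 0 and 6) the baseline weight is 0.25 year, so its direct contribution has an SE of 0.0032 QALY. The 95% half-width is 1.96 × 0.0129 × 0.25 = 0.0063. For SDs of 0.10 to 0.15 it is 0.0053 to 0.0079. That is not negligible beside a linear-path effect of 0.010.

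**The case against.** Several points on the other side are sound.

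- **The schedule is unseen.** A reader might infer that the SF-6D is not collected at all, or only at month 6. The documents do not support that. Fig. 3 may schedule it. The survey lists are also visibly incomplete: the baseline list omits depressive symptoms, although every participant has a qualifying EPDS score. What stands is that the text conflicts and must be reconciled.
- **Randomisation.** A reader might infer that no valid comparison is possible. Randomisation makes baseline utilities equal in expectation, so the month-6 difference is a valid contrast at that time. It could be turned into QALYs under a stated path assumption, but the article states none.
- **The conversion formula.** The article does not say that month-6 utility is multiplied by 0.5 year. That row in the table is one possible conversion, and the exact formula could reasonably sit in a fuller document. The time point, however, is stated here.
- **The error is not always large.** If the difference is fully present from month 1, multiplying by 0.5 year gives 0.020 against 0.0183, about 9% too high.
- **Baseline imbalance.** A reader might infer that it passes straight into the result. In a month-6-only calculation baseline utility does not enter. It acts only through its correlation with month-6 utility and is part of ordinary sampling error. A carry-through of 0.0064 QALY (0.0129 × 0.5) would need a correlation of 1. Adjustment is a gain in precision and a protection against chance imbalance, and validity does not hinge on it.

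The description of utility as derived from QALYs is a slip of wording, since the next sentence uses the QALY difference correctly.

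**Conclusion.** The point holds for the text as written. The cost-effectiveness section ties QALYs to the SF-6D at month 6 alone, and neither survey list names the instrument. One month-6 utility cannot determine the six-month QALY difference. Under the assumed 0.04 difference the gain runs from 0.005 to 0.025 QALY depending on the path, and a benefit that fades before month 6 is lost. These sizes rest on assumed utilities and equal baselines, and they show sensitivity to the path rather than a predicted error.

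Fig. 3 could settle whether earlier measurements are taken. Even then, the cost-effectiveness section would still name month 6 only, and the survey lists would need correcting. The primary outcome, its sample size and the EPDS-based ICER are untouched. This is a should-fix for the cost-utility analysis.

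**What to change.** 1. Name the SF-6D in the baseline survey and in the existing 1-, 3- and 6-month surveys, and make Table 1, the survey lists, the cost-effectiveness section and Fig. 3 agree.
2. State that each woman's QALYs are the area under her utility curve over 0.5 year by the trapezoid rule, and correct the wording so that QALYs are derived from utilities.
3. Estimate the arm difference in QALYs by regression adjusted for baseline utility.

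The cost is somewhat longer surveys at four existing contacts, with follow-up mostly by telephone, plus a few lines of analysis text. The article does not give the form or length of the SF-6D questionnaire to be used, so the added time cannot be stated. The change is best made before enrolment, because baseline utilities cannot be recovered later. For any woman without earlier measurements, the report should state the path assumption and show the range of results under alternatives.
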